### Strategies to improve adherence to interventions {11c}

Participants will be issued with a dosing diary at their baseline visit to record the number of tablets taken and to indicate any missed doses (and reasons for non-adherence). However, participants will also be asked to return any unused trial drug and a pill count conducted. A cumulative total of 28 missed doses (i.e. 14 days of incomplete doses) over the entire treatment period will trigger a review by the Chief Investigator (CI) for consideration of participant withdrawal.

### Relevant concomitant care permitted or prohibited during the trial {11d}

A requirement for trial eligibility is treatment with a MS DMT. It is expected that participants continue to receive this medication, provided and prescribed by their original physician and neurology service. However, this is not a condition of continued participation. If participants experience AEs or a lack of efficacy of their treatment and wish (or are advised) to terminate or change treatment, they are free to do so.

Throughout the trial, investigators may prescribe any concomitant medications or treatments deemed necessary to provide adequate supportive care, save for those specified in the exclusions for trial participation. Any medication, other than the trial medication taken during the trial, will be recorded in the case report form (CRF).

Prohibited concomitant medications during the trial are hypoglycaemic agents, oxybutynin, monoamine oxidase inhibitors, hypnotics, high-dose opiates, fampridine and 4-aminopyridine. We will advise participants to avoid alcoholic drinks for the duration of the trial.

### Provisions for post-trial care {30}

Participation in the trial ends following completion of the week 28 visit (or earlier in the case of those withdrawing from the trial). Participants will return to routine NHS care, and any unresolved serious adverse events (SAEs) will be followed up clinically until resolution outside of this trial. The University of Cambridge has arranged insurance for negligent harm caused as a result of protocol design and for non-negligent harm arising through participation in the clinical trial. Participants will be reimbursed for travel and parking costs incurred by completing claim forms (with receipts) at each trial visit. There is no provision for participants to continue on metformin and clemastine—or to start on active treatment—following the end of this trial.

## Outcomes {12}

### Primary outcome: full-field VEP

The primary outcome measure of CCMR Two will be the change in the P100 latency of the full-field VEP between baseline and week 26 for each eye with a baseline latency of ≥ 118 ms. The latter timepoint, 2 weeks removed from the end of treatment (week 24), has been selected to ensure that more than five half-lives of the IMP have passed prior to the final VEP assessment; in this way any change in latency cannot be attributed to a direct effect of the IMP on conduction velocity (making any changes more specific to variation in myelination).

### Secondary outcomes: multifocal VEP

A secondary outcome of the trial is to interrogate the change in multifocal VEP latency, between baseline and week 26, for those eyes with delayed latency (≥ 151 ms) at baseline. While full-field VEP is a sensitive tool for detecting latency abnormalities in the visual pathway [50] and has been deployed in several remyelination trials [23, 24], limitations of full-field VEP include macular overrepresentation in the visual cortex and the propensity for conventional electrode placement (frontal-occipital) to favour the response from the lower visual field; small and localised areas of demyelination are often not detected [51–53]. Additionally, as the upper visual field projects to the lower bank (lingual gyrus) of the sulcus calcarinus, while the lower visual field projects to the upper bank (cuneus gyrus), the full-field VEP is susceptible to the phenomenon of phase cancellation: the cortical dipoles from the upper and lower hemifields are almost opposite, resulting in a cancellation effect on amplitude in an unaffected eye [54]. Consequently, a corollary of demyelination in the visual pathway can be that the recorded signal appears larger due to less cancellation effect. Multifocal VEP (MF-VEP) mitigates against these problems by simultaneously stimulating multiple individual regions of the visual field and extracting the unique signals corresponding to each. This allows for a potentially more precise analysis of latency and amplitude abnormalities in people with optic neuropathy [55–57]. MF-VEP has previously been deployed in a substudy of the RENEW trial [58] and is now being used in remyelination trials as an outcome measure, such as in the clinical trial of nanocrystalline gold (NCT03536559).

### Secondary outcomes: magnetisation transfer ratio

The co-secondary outcome is the change in lesional MTR, between baseline and week 26, for MS lesions stratified by location and the tissue-specific cohort baseline lesional MTR values. MTR correlates with histopathological demonstration of myelin in MS lesions [59] and our analyses have been selected to account for evidence that the degree of remyelination in an MS lesion is dependent both on its location, potentially being greatest in the grey matter [60–63], and the degree of its demyelination at baseline [27]. We have prioritised chronic lesions in our analysis as remyelination trials centred on acute lesions require frequent MRI scans and large numbers of participants [26].

### Secondary outcomes: safety and tolerability

Each trial visit after the point of informed consent will capture data on adverse events (AEs), which will be evaluated by the investigator to establish seriousness and any relationship with the IMP (causality). AEs and withdrawals will be reported.

### Exploratory outcomes: visual pathway

The trial will evaluate the effects of metformin and clemastine on other measures of neuroprotection and visual function measured both before and after the treatment period: (i) the change in the amplitude of the full-field VEP, between baseline and week 26; (ii) the change in the amplitude of the multifocal VEP, between baseline and week 26; (iii) the change in visual acuity (change in numbers of letters read on the Sloan 100%, 2.5% and 1.25% acuity charts (and corresponding LogMAR score)), between baseline and week 28; (iv) the change in colour vision (change in protan, deutan, and tritan confusion lines at the Cambridge Colour Test), between baseline and week 28; (v) the change in visual fields (change in mean deviation and pattern deviation), between baseline and week 28; and (vi) the change in RNFL and ganglion cell inner plexiform layer thicknesses, between screening and week 28 [64]. In subsidiary research, to be analysed outside of the final study report, we will test the change in saccadic latency parameters [65], between screening and week 28 and the change in latencies of the N75 and N145 latencies of the full-field VEP, between baseline and week 26.

### Exploratory outcomes: MRI

We will report the change in T2 lesion load between baseline and week 26 as a measure of inflammatory activity (albeit potentially clinically silent). Using MTR, the effects of metformin and clemastine will be compared at a voxel level, lesion subcomponent level, and at the whole lesion level (including after stratifying lesions by type). These analyses will be modelled on our previous research which showed remyelination in response to bexarotene varied within and between lesions [63]. A final exploratory outcome will report the change in different MRI biomarkers of remyelination (described below).

### Exploratory outcomes: clinical measures and blood biomarkers

CCMR Two will assess the change in disability (measured by the EDSS step) between week 26 and the screening visit. Blood will be stored (optional) for future research on blood-based biomarkers of remyelination. Change in serum neurofilament light chain, between baseline and week 26, has been included for reporting in the statistical analysis plan.

### Definition of eligible eyes for primary, secondary and exploratory outcome measures

As a point of clarification, as per the selection criteria, eligible eyes will have a RNFL on spectral-domain OCT ≥ 70 μm. In the circumstance of a participant having delayed VEP latencies in both eyes, but RNFL thickness < 70 μm in one of those eyes, only the qualifying (≥ 70 μm) eye would be included in the analysis. Additionally, to be included in the multifocal VEP outcome measure analysis, an eye must additionally have 28 or more segments with recordable signal (at least half of the 56 recordable segments).

### Participant timeline {13}

The screening visit will be divided into two sets of assessments. On the first, after signing of the informed consent form (ICF), the trial team will review the participant’s medical history, imaging and records to confirm the diagnosis of RRMS [32] and their eligibility for inclusion (Table 1). Participants will then have their screening VEP assessments to ensure there is detectable demyelination in the visual pathway. Our data suggest that in the region of 25–50% of potential participants will not pass screening at this point; in the ReBUILD trial, it is noteworthy that 75 failed screening on this same criterion to yield 50 eligible participants [23]. If these assessments are satisfied, the individual would then be invited to return for a second series of screening investigations including blood tests, EDSS assessment, and OCT to ensure the criteria outlined in Table 1 are similarly met; a much lower attrition rate is anticipated at this point.

Following documented permission from the potential participant when signing the ICF, their usual treating neurologist and/or general practitioner (GP) will be contacted to detail their involvement in the trial; if they are not able to be randomised after attending screening, reasons for this will be communicated to both the participant and referring clinician. We will also maintain a log of all who are ineligible for the trial and all eligible participants that will not be randomised because they declined participation. This process will enable generalisation of the trial results in accordance with the Consolidated Standards of Reporting Trials (CONSORT) guidelines of 2010 [66].

Baseline assessments will take place after randomisation and up to 2 weeks prior to commencement of IMP. After the baseline visit, the MRI will be reviewed for quality control. If this passes, the participant will start IMP within 2 weeks as outlined. In the unlikely event of the MRI not passing quality control, it is possible that we would require a repeat MRI scan. This would be scheduled at least 2 days prior to the commencement of IMP.

Participants receive 24 weeks of treatment. Participants are to be seen at Addenbrooke’s hospital after 4 weeks, 12 weeks, 26 weeks, and a final visit at 28 weeks from treatment initiation. A visit window for week 4 and week 12 visits of ± 7 days will be permitted where scheduling participant visits is difficult or in the event of ill health or transport issues. A visit window of + 7 days will be permitted for the week 26 visit if a similar problem arises. A visit window of ± 14 days will be permitted for the week 28 visit.

A summary of participant assessments is presented in Table 2.

**Table 2 Tab2:** Schedule of assessments for CCMR Two

**Assessment**	**Screening 1**	**Screening 2**	**Baseline**	**Treatment phase**						Week 26	Week 28
**Clinic visit number**	**1**	**2**	**3**	No visit	No visit	**4**	**5**	No visit	No visit	**6**	**7**
**Visit window**	**Day − 70 to − 14**	**Day − 70 to − 14**	**Day − 14 to − 7**	Day 1	Day 15	**Week 4 (± 7 days)**	**Week 12** **(± 7 days)**	Week 24	Week 24	**Week 26 (+ 7 days)**	**Week 28 (± 14 days)**
Informed consent	X			**Start IMP**				**Stop IMP**			
Eligibility assessments	X	X									
Medical and MS history	X										
Physical examination^1^		X								X	
EDSS assessment		X								X	
Concomitant medication check	X		X			X	X			X	
Randomisation		X^2^									
Adverse event assessments		X	X			X	X			X	X
IMP dispensing			X			X	X				
IMP dose increase					X	X					
IMP compliance check						X	X			X	
Safety bloods		X				X	X			X	
Optional research bloods (for storing serum, plasma and whole blood)		X					X			X	
Optional stool sample			X			X			X		
12 lead ECG		X									
Pregnancy test (women of childbearing potential only)		X	X			X	X			X	
Full-field VEP	X		X				X			X	
Multifocal VEP	X		X				X			X	
OCT		X									X
Visual fields			X								X
Visual acuity			X				X				X
Eye tracking		X									X
MRI imaging			X							X^3^	

Trial specific activity is shown for each visit; see text for additional information. ^1^Physical examination to include: height (screening only), weight, pulse, and blood pressure. ^2^Randomisation only to be completed once all screening assessments are complete and eligibility confirmed. ^3^The second MRI can be undertaken at either week 26 (or week 28 visit, if necessary). *MS*, multiple sclerosis; *EDSS*, expanded disability status scale; *IMP*, investigational medicinal product; *ECG*, electrocardiogram; *VEP*, visual evoked potential; *OCT*, optical coherence tomography; *MRI*, magnetic resonance imaging

### Sample size {14}

The primary endpoint is the change in the P100 latency of the VEP between baseline and week 26 for each eligible eye. An average reduction of 3.0 ms/eye in VEP at week 26 between metformin + clemastine (research arm) and placebo (control arm) will be an important treatment effect to detect. There is no evidence for an interaction of VEP between eyes. With a 5% significance level (two-sided), 80% power, and a common standard deviation of 5 ms, 45 eyes in each arm are required to detect a difference of 3.0 ms/eye in the mean change of VEP at week 26 from baseline between the two treatment groups (nQuery). The common standard deviation of 5 ms was based on the ReBUILD study [23], which was approximately 4.1 ms, and added around 20% (4.1 × 1.20 = 4.92) more variation. Allowing for 10% non-compliance, that is 50 eyes per arm: it was originally planned to recruit 50 participants. Following the planned interim analysis meeting held on 28/06/23, the trial sample size increased to 70 participants as around 50% of participants had only one eligible eye at screening. The Independent Data Monitoring Committee (IDMC) supported the plan to increase recruitment to reach the required eligible eyes.

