**Methods:**

Participants with relapsing-remitting MS (RRMS) will be randomised 1:1 to the combination of metformin and clemastine or matched placebos and followed for 24 weeks of treatment. All participants must be stable on a disease-modifying therapy and have evidence of chronic stable optic neuropathy in at least one eye (defined by P100 latency of the visual evoked potential (VEP) ≥ 118 ms, and the absence of a history of acute optic neuritis in the preceding 2 years). The primary outcome measure will be the change in the P100 latency of the full-field VEP between baseline and week 26. It is planned to recruit a total of 70 participants. This will have 80% power to detect a reduction of 3 ms in VEP P100 latency between the two treatment groups. Secondary outcome measures will examine the change in multifocal VEP and the change in lesional magnetisation transfer ratio (MTR) for lesions stratified by location and tissue-specific cohort baseline lesional MTR values.

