### Primary outcome measure: full-field VEP

The primary analysis of this trial will compare the mean change in the P100 latency of the full-field VEP from baseline and week 26, between metformin + clemastine (research arm) and placebo (control arm). This will be based on eligible eyes with delayed (≥ 118 ms) baseline P100 latency. Eligible eyes will additionally have RNFL thickness ≥ 70 μm (see outcomes Sect. 12 for the definition of eligible eyes). A mixed-effect model will be used for eyes nested within participants, with random effects for participants and fixed effects for treatment allocation at randomisation, baseline P100 latency and stratification factors.

Fixed effects: treatment allocation, baseline P100 latency, age at consent (≤ 40 years vs > 40 years), sex (male vs female), baseline MS DMT treatment category (1 vs 2) [5], screening EDSS (≤ 4.0 vs > 4.0).

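### The 80% power stated for 70 participants counts a participant's two eyes as independent, though participants are randomised and the primary model clusters eyes; power should be stated conditional on the inter-eye correlation

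*Protocol article*

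**What the plan says.** The section Sample size {14} sets these inputs: "With a 5% significance level (two-sided), 80% power, and a common standard deviation of 5 ms". It concludes that "45 eyes in each arm are required to detect a difference of 3.0 ms/eye in the mean change of VEP at week 26". The SD starts from the earlier clemastine trial, "which was approximately 4.1 ms, and added around 20% (4.1 × 1.20 = 4.92) more variation", and is rounded up to 5 ms. The loss step reads "Allowing for 10% non-compliance, that is 50 eyes per arm", and the original plan was 50 participants. The number later rose to 70 because about half of participants had only one eligible eye. On dependence between eyes the section says only "There is no evidence for an interaction of VEP between eyes".

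The abstract (Methods) plans 70 participants and states: "This will have 80% power to detect a reduction of 3 ms in VEP P100 latency between the two treatment groups".

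Sequence generation {16a} assigns participants, not eyes, in a 1:1 ratio. The primary analysis reads: "A mixed-effect model will be used for eyes nested within participants, with random effects for participants".

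**The concern.** Two counts show that each second eye was taken as a full independent observation. First, 50 participants were originally meant to supply the 100 required eyes. Second, the rise to 70 was made only to restore the number of eligible eyes. No inter-eye correlation or design effect appears.

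Both eyes of a participant are always in the same arm. If their changes are positively correlated, the second eye adds less than one eye of information. The planned mixed model allows for this; the sample size does not. Finding no evidence of an interaction between eyes is a different statement from finding that changes in the two eyes are uncorrelated, and absence of evidence does not make the correlation zero. Some positive correlation is plausible: the eyes share drug exposure and visit, and the article describes one midline recording channel for the full-field VEP. Its size is unknown.

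At stake is the headline power for the primary endpoint. A null result read against an unqualified 80% for 3 ms could be taken as stronger evidence against that effect than the design supports.

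**Working it through.** **Inputs from the article.** Two-sided alpha 0.05; difference 3.0 ms; SD 5 ms (source value 4.1 ms); 10% loss; 70 participants randomised 1:1, so 35 per arm; about half with one eligible eye, so 1.5 eyes per participant.

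**Input not in the article.** The correlation rho between the changes in a participant's two eyes. I show 0, 0.3, 0.5 and 0.7; these values are assumptions.

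**Step 1: reproduce the stated figure.** A two-sample t-test on independent eyes (noncentral t) gives 80.4% power with 45 eyes per arm and 79.5% with 44. So 45 is correct for independent eyes, and 45 / 0.9 = 50.

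**Step 2: effective eyes.** The mean of two eyes has variance SD² × (1 + rho) / 2, so a pair counts as 2 / (1 + rho) eyes. With P participants per arm, half of them with two eyes:

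N_eff = P × [0.5 + 0.5 × 2 / (1 + rho)]

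With the plan's loss P = 35 × 0.9 = 31.5; without loss P = 35. At rho 0.5 with loss, N_eff = 31.5 × (0.5 + 0.5 × 1.333) = 36.75.

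**Step 3: power at SD 5 ms.** Noncentrality = 3 / (5 × √(2 / N_eff)), with 2P − 2 degrees of freedom (61 with loss, 68 without). At rho 0.5 with loss: 3 / (5 × √(2 / 36.75)) = 2.57, which gives 71.6%.

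| rho | N_eff per arm, 10% loss | Power, 10% loss | N_eff per arm, no loss | Power, no loss |
|---|---|---|---|---|
| 0 | 47.25 | 81.9% | 52.5 | 85.8% |
| 0.3 | 40.0 | 75.2% | 44.4 | 79.6% |
| 0.5 | 36.8 | 71.6% | 40.8 | 76.2% |
| 0.7 | 34.3 | 68.6% | 38.1 | 73.3% |

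Power drops below 80% once rho exceeds about 0.08 with the loss, or about 0.28 without it.

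**Step 4: difference detectable with 80% power at SD 5 ms.** For rho 0.3, 0.5 and 0.7: 3.18, 3.32 and 3.44 ms with loss; 3.02, 3.15 and 3.26 ms without.

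**Step 5: the SD margin.** At SD 4.1 ms with 10% loss, the same formula gives 89.6%, 87.0% and 84.6% at rho 0.3, 0.5 and 0.7. The detectable difference is proportional to the SD, so power for 3 ms is exactly 80% when SD = 5 × 3 / (detectable difference at SD 5). With loss this is 15 / 3.18 = 4.7, 15 / 3.32 = 4.5 and 15 / 3.44 = 4.4 ms. Without loss it is 15 / 3.02 = 5.0, 15 / 3.15 = 4.8 and 15 / 3.26 = 4.6 ms.

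**The case against.** The strongest reply is that the plan holds a reserve of similar size. Raising the SD from 4.1 to 5 ms multiplies the variance by (5 / 4.1)² = 1.49, and with 10% loss power at SD 4.1 stays at 85-90% for rho 0.3-0.7. Baseline latency is also a covariate, and any gain from it is not counted. This stands as a limit on the size of the shortfall. It does not support the sentence as written, because the article assigns the SD margin to extra variation, not to clustering, and the calculation takes 80% at SD 5.

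It is also fair that rho is not known from the article, and that a random participant effect allows for correlation without showing that it is large. This stands too, and it rules out the stronger reading that the design delivers 69-75%. That range needs both an assumed rho of 0.3-0.7 and the full 10% loss. The article expects missing primary data to be rare, lets early withdrawals be replaced and asks people who stop treatment to stay for assessments, so the no-loss range of 73-80% has at least equal support.

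A reader might also infer that non-compliers kept in the mITT population dilute the effect, so that dividing by 0.9 is too small an inflation. Any figure for this needs an assumed effect in those who stop. Zero effect would be an extreme choice: mITT members have had more than 2 months of treatment, and the article reports that in the earlier trial the clemastine effect persisted after 90 days of treatment followed by placebo. The documents do not support that point, and it is not made here.

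**Conclusion.** The point holds as a matter of an unsupported assumption behind a headline figure. The figures of 45 and 50 eyes per arm are arithmetically right, but the 80% for 70 participants at SD 5 ms holds only if rho is at most about 0.08 with the plan's loss, or about 0.28 without it. For assumed rho of 0.3-0.7, power is about 69-75% with loss and 73-80% without. At rho 0.3 without loss the shortfall is under half a percentage point. Below 80% also requires that much of the SD margin is used up: a true SD above roughly 4.4-4.7 ms with loss, or 4.6-5.0 ms without, over the same range of rho.

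It would be wrong to infer that the primary analysis is invalid. The planned model accounts for the clustering, so the estimate, its confidence interval and the type I error are not in question. Severity is moderate.

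**What to change.** - Keep 70 participants; recruitment closed in October 2024.
- In Sample size {14}, replace the sentence on interaction between eyes with a statement that the calculation treats eyes as independent and that no inter-eye correlation of changes was available.
- In that section and in the abstract, give power conditional on rho at SD 5 ms: about 82%, 75%, 72% and 69% at rho 0, 0.3, 0.5 and 0.7 with 10% loss, and about 86%, 80%, 76% and 73% without. Add the detectable difference for rho 0.3-0.7 (about 3.2-3.4 ms with loss, 3.0-3.3 ms without) and the result at SD 4.1 ms (about 85-90% with loss).
- If the data are still blinded, estimate rho from the pooled data and state power at that value. If not, report the observed rho with the result. A pooled estimate runs slightly high if treatment works: a 3 ms effect adds 3² / 4 = 2.25 ms² to both the variance and the covariance, so a within-arm rho of 0.3 at SD 5 would appear as (7.5 + 2.25) / (25 + 2.25) = 0.36.

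The cost is wording and one descriptive estimate. Design, model and endpoint do not change, but a stated figure becomes less favourable.
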